# Selumetinib in combination with dexamethasone for the treatment of relapsed/refractory RAS-pathway mutated paediatric and adult acute lymphoblastic leukaemia (SeluDex): study protocol for an international, parallel-group, dose-finding with expansion phase I/II trial

**DOI:** 10.1136/bmjopen-2021-059872

**Published:** 2022-03-04

**Keywords:** clinical trials, leukaemia, adult oncology, paediatric oncology

## Abstract

**Introduction:**

Event-free survival rates at 15 years for paediatric patients with relapsed/refractory acute lymphoblastic leukaemia (ALL) are 30%–50%, with 5-year survival for adult patients only 20%. Many patients with newly diagnosed and relapsed ALL harbour somatic RAS-signalling activation mutations. Induction therapy for ALL involves steroids, with preclinical data suggesting the combination of dexamethasone with the MEK1/2 inhibitor, selumetinib (ARRY-142886) has a synergistic anticancer effect.

**Methods and analysis:**

The SeluDex trial is an international, parallel-group, dose-finding with expansion, phase I/II trial to assess the selumetinib/dexamethasone combination in adult and paediatric patients with relapsed/refractory, RAS pathway mutant ALL. The Cancer Research UK Clinical Trials Unit at University of Birmingham is the UK Coordinating Centre, with national hubs in Copenhagen, Denmark; Monza, Italy; Münster, Germany; Paris, France; and Utrecht, Netherlands. Patients with morphologically proven relapsed/refractory or progressive B-cell precursor or T-cell ALL, with demonstrated RAS pathway activating mutations are eligible. Adult patients are >18 years old, ECOG <2 and paediatric <18 years old, Lansky play scale ≥60% or Karnofsky score ≥60%. Phase I primary objective is the recommended phase II dose of selumetinib as defined by occurrence/non-occurrence of dose limiting toxicities using the continual reassessment method; phase II will evaluate preliminary antileukaemic activity of the combination, as defined by morphological response 28 days post-treatment using a Bayesian approach. Target recruitment is between 26 and 42 patients (minimum 13 and maximum 21 per group), depending the number of phase I patients included in phase II.

**Ethics and dissemination:**

Medical ethical committees of all the participating countries have approved the study protocol; initial (UK) ethics approval (17/YH/0123) was granted by Yorkshire & The Humber—Leeds West Research Ethics Committee. Participants are required to provide written informed consent/assent. Results will be disseminated through national and international presentations and peer-reviewed publications.

**Trial registration number:**

ISRCTN92323261.

Strengths and limitations of this studyNovel combination of the MEK1/2 inhibitor, selumetinib, with dexamethasone.Seamless phase I/II Bayesian trial design with a continual reassessment method for dose escalation in phase I.Parallel cohort trial design of adult and paediatric patients within one protocol.Availability of CAR T-cell therapy since this trial started recruitment has competed for the same patient population, however, SeluDex offers a bridging treatment option for patients awaiting CAR T-cell therapy outside clinical studies or at relapse after CAR-T treatment.

## Introduction

Acute lymphoblastic leukaemia (ALL) is the most common childhood cancer, representing 26.8% of all childhood malignancies.^1^ While the overall cure rate for newly diagnosed paediatric ALL is approaching 90%, children with relapsed ALL (rALL) are still facing a poor outlook, with reported overall event-free survival rates at 15 years of 30%–50%,^2^ and rALL remains a frequent cause of death.

In adults, the frequency of ALL is significantly lower, with an incidence of around one per 100 000.^3^ ALL in adulthood has proven to be more challenging to treat compared with childhood ALL, with the disease being more resistant to chemotherapy, and patients have a reduced treatment tolerance especially in the elderly population. Five-year overall survival rate remains at ~20% among adult patients aged ≥60 years, even though improvement has been observed since 1980.^4^

Data demonstrate that mutations activating the RAS-signalling cascade (NRAS, KRAS, FLT3 and PTPN11 and cCBL) are highly prevalent at both diagnosis and relapse of paediatric B-cell precursor ALL (incidence 38% at relapse), and are associated with high-risk features such as early relapse, central nervous system (CNS) involvement and chemoresistance.^5^ Neurofibromin (NF1) copy number variants, point mutations or intragenic deletions have been reported in approximately 4% of T-cell ALL, 14% of early T-cell precursor (ETP), ~30% of low hypodiploidy, 2% high risk of B-cell ALL and 75% of relapsed hypodiploid ALL.^6–10^ BRAF point mutation incidence is approximately 3% in T-cell ALL, 4% in ETP and 0.5% in high-risk B-cell ALL.^7–9^ IKZF2 and IKZF3 deletions which have recently been shown to activate the RAS-pathway have an incidence of approximately 18% in hypodiploid ALL.^11^ IL7Rα point mutations, deletions and in-frame alterations are found in approximately 9% of T-ALL,^12 13^ and JAK1 point mutations are found in approximately 5% of T-ALL.^14^

Selumetinib is a potent and selective allosteric MEK1/2 inhibitor that has been evaluated in phase II/III clinical trials for several cancers, including BRAF mutation-positive melanoma,^15^ metastatic uveal melanoma,^16^ pancreatic,^17^ colorectal^18^ and KRAS mutation-positive NSCLC.^19^ Preclinical models suggest a synergistic effect when selumetinib and dexamethasone were combined in an orthotopic mouse model with three different RAS-pathway mutant ALL primagrafts and a mechanistic basis to the synergy was identified involving heightened levels of the proapoptotic BIM protein.^20^ However, the combination of selumetinib and dexamethasone has not been evaluated in a clinical trial setting.

The aim of the SeluDex trial is to determine the dose of selumetinib to use in combination with dexamethasone in adult and paediatric patient populations, and to assess the preliminary antileukaemic properties of the combination in each group of patients.

## Methods and analysis

### Study design

The SeluDex trial is a parallel-group, non-randomised, open-label, dose-finding with expansion, phase I/II clinical trial. As an early phase dose-finding and signal-seeking trial, a comparator arm was not included. Group A (adult patients) and group P (paediatric patients) will both receive selumetinib in combination with a standard dose of dexamethasone (figure 1). Patients will be recruited from public hospitals. The Cancer Research UK Clinical Trials Unit (CRCTU) at University of Birmingham is the UK Coordinating Centre, with national hubs in Copenhagen, Denmark; Monza, Italy; Münster, Germany; Paris, France; and Utrecht, Netherlands. The national coordinating and participating centres are all part of the Innovative Therapies for Children with Cancer in Europe consortium (ITCC).

**Figure 1 F1:**
[figure not shown]
SeluDex trial schema SeluDex trial schema showing the patient pathway highlighting screening, trial entry, treatment and follow-up. ALL, acute lymphoblastic leukaemia; BD, two times a day; PD, pharmacodynamic; PIS, patient information sheet; PK, pharmacokinetic.

This trial aims to recruit between 26 and 42 patients (minimum of 13 and maximum of 21 in each group), depending on how many phase I patients are included also in phase II. The recruitment period is expected to be 4 years, with participants followed up for 1 month after a maximum of 6 treatment cycles. WHO Trial Registration Data Set is attached in online supplemental appendix 1.

10.1136/bmjopen-2021-059872.supp1Supplementary data

### Patient and public involvement

Patients and public were not involved in the design and conduct of this research but will be consulted in the reporting and dissemination of its outputs.

### Patient selection

The two parallel patient groups in SeluDex, group A (Adult) and P (Paediatric), have similar but discrete eligibility criteria. The main eligibility criteria are detailed in boxes 1 and 2, respectively. The screening process is the same for both groups. Eligibility for trial entry is dependent on screening of a bone marrow (BM) aspirate to confirm morphological relapse and RAS-pathway mutation status. Peripheral blood may also be used in the case of a dry tap if white cell counts >50×10^9^ /L. Centralised genetic analysis in the UK at Northern Genetics Service’s laboratories in Newcastle upon Tyne will identify the presence of a RAS-pathway activating mutation (key exons of NRAS, KRAS, FLT3, PTPN11 or cCBL mutation). A primary screen of the two most common mutations (NRAS and KRAS) will be performed first and if no mutations are found a secondary screen of the remaining mutations (FLT3, PTPN11 and cCBL) will be performed. Alternatively, locally obtained genetic results may be used to confer RAS-pathway mutation status if tested in a clinically compliant laboratory using a clinically validated test with material from the current relapse. Laboratories will be approved by the Trial Office to use local NRAS, KRAS, FLT3, PTPN11, cCBL, NF1, BRAF, IKZF2, IKZF3, IL7Rα or JAK1 testing.

Box 1Main eligibility criteria for Group AMain inclusion criteriaMorphologically proven relapsed/refractory (M2 or M3 marrow; ≥1 st relapse) or progressive B cell precursor or T-acute lymphoblastic leukaemia (ALL) with demonstrated RAS pathway activating mutations (NRAS, KRAS, FLT3, PTPN11, cCBL, neurofibromin 1, BRAF, IKZF2, IKZF3, IL7Rα or JAK1) identified during the trial screening process.B cell precursor patients must either:Have received CAR-T cell therapy, orBe awaiting CAR-T cell therapy, orBe considered ineligible for CAR-T cell therapy.≥18 years of age.Adequate renal function: Serum creatinine <1.5 × upper limit of normal (ULN).Patient is able to swallow selumetinib capsules whole.Eastern Cooperative Oncology Group (ECOG) ≤2.Women of childbearing potential must have a negative pregnancy test.Patients who are women of childbearing potential and male patients with partners who are women of childbearing potential must agree to use appropriate contraception (see section 7.9.3 for definition) while on trial.Written informed consent.Patients must have a body surface area ≥0.55 m^2^.Main exclusion criteriaALL without presence of RAS-pathway activating mutations.Mature B-cell leukaemia and Philadelphia positive ALL.Prior exposure to MEK, RAS or RAF inhibitors.Any unresolved toxicity ≥Common Terminology Criteria for Adverse Events grade 2 from previous anticancer therapy, except for alopecia.Cardiac conditions as follows:Prior or current cardiomyopathy including but not limited to the following:Known hypertrophic cardiomyopathy.Known arrhythmogenic right ventricular cardiomyopathy.Even if full recovery has occurred, previous moderate or severe impairment of left ventricular systolic function (LVEF <45% on echocardiogram, ECHO).Severe valvular heart disease.Severe congenital heart disease.Uncontrolled hypertension: Blood pressure ≥150/95 mm Hg despite medical therapy.Baseline (LVEF) below the lower limit of normal or <55% measured by ECHO.Acute coronary syndrome within 6 months prior to trial registration.Uncontrolled Angina—Canadian Cardiovascular Society grade II–IV despite medical therapy.Symptomatic heart failure New York Heart Association class II–IV, prior or current cardiomyopathy, or severe valvular heart disease.Atrial fibrillation with a ventricular rate >100 bpm on ECG at rest.QT Interval Corrected Using Fridericia's Formula (QTcF) >450ms in male patients or ≥460ms in female patients, or other factors that increase the risk of QT prolongation.

Box 2Main eligibility criteria for Group PMain inclusion criteriaMorphologically proven relapsed/refractory (M2 or M3 marrow; ≥2nd relapse) or progressive B cell precursor or T-Acute Lymphoblastic Leukaemia (ALL) with demonstrated RAS pathway activating mutations (NRAS, KRAS, FLT3, PTPN11, cCBL, NF1, BRAF, IKZF2, IKZF3, IL7Rα or JAK1) identified during the trial screening process.B cell precursor patients must either:Have received CAR-T cell therapy, orBe awaiting CAR-T cell therapy, orBe considered ineligible for CAR -T cell therapy.<18 years of age.Adequate renal function:≤5 years: serum creatinine <0.8 mg/dL or 70 µmol/L µmol/L.>5 years but ≤10 years: serum creatinine <1 mg/dL or 88 µmol/L µmol/L.>10 years but ≤15 years: serum creatinine <1.2 mg/dL or 106 µmol/L µmol/L.>15 years: serum creatinine <1.5 mg/dL or 132 µmol/L µmol/L.The patient is able to swallow selumetinib capsules whole.Lansky play scale ≥60% or Karnofsky scale ≥60%.Women of childbearing potential must have a negative pregnancy test.Patients who are women of childbearing potential and male patients with partners who are women of childbearing potential must agree to use appropriate contraception (see section 7.9.3 for definition) whilstwhile on trial.Written informed consent.Patients must have a body surface area ≥0.55 m^2.^Main exclusion criteriaALL without presence of RAS-pathway activating mutations.Mature B-cell leukaemia and Philadelphia positive ALL.Prior exposure to MEK, RAS or RAF inhibitors.Any unresolved toxicity ≥Common Terminology Criteria for Adverse Events grade 2 from previous anticancer therapy, except for alopecia.Cardiac conditions as follows:Prior or current cardiomyopathy including but not limited to the following:Known hypertrophic cardiomyopathy.Known arrhythmogenic right ventricular cardiomyopathy.Even if full recovery has occurred, previous moderate or severe impairment of left ventricular systolic function (SF <29% but excluding transient impairments due to, for example, anaemia/sepsis or results not thought to represent a true reflection of cardiac function).Severe valvular heart disease.Severe congenital heart disease.Uncontrolled hypertension: Blood pressure ≥95 th percentile for age, height and gender.Baseline SF <29%.Atrial fibrillation with a ventricular rate >130 bpm on ECG at rest.QT Interval Corrected Using Fridericia's Formula (QTcF) >450 ms in patients <12 years or ≥460 ms in patients ≥12 but <18 years.Ophthalmological conditions as follows:Current or history of retinal pigment epithelial detachment/central serous retinopathy or retinal vein occlusion.Intraocular pressure (IOP) >21 mm Hg or uncontrolled glaucoma (irrespective of IOP).Pregnant and breastfeeding femalesKnown severe hypersensitivity to selumetinib, dexamethasone or combination medications or any excipient of these medicinal products, or history of allergic reactions attributed to compounds of similar chemical or biological composition to selumetinib.

### Consent

Consent is requested by an investigator at two time points. A pretrial genetic assessment consent allows for central/local analysis of a sample at screening to assess RAS mutation status, and the main trial consent, which is performed once mutation status is confirmed and a treatment slot is reserved. The main trial consent will be for either the phase I dose finding, or phase II dose expansion. Furthermore, age-specific consent/assent forms are available for patients over 16 years of age, and parents/legal guardians of paediatric patients (as appropriate according to age and national legislation). An example of the main consent form for adult patients is available in online supplemental appendix 2. Age-specific patient information sheets (PISs) are available for patients over 16 years of age, parents/legal guardians of paediatric patients, and teenage patients aged 13–15 years. As an example, the adult PIS is available in online supplemental appendix 3.

10.1136/bmjopen-2021-059872.supp2Supplementary data

10.1136/bmjopen-2021-059872.supp3Supplementary data

### Interventions

The dosing schedule for the dose-finding phase of the trial is summarised below for each group and detailed in specified tables. Treatments are given over a 28-day cycle and will be continued for six cycles unless one or more of the following is observed; intolerable toxicity, confirmed disease recurrence or progression, pregnancy, severe non-compliance to protocol, development of any trial-specific criteria for discontinuation (not reaching at least a partial response (PR) at cycle 1, day 28), or investigator decision, for example, if the patient requires a prohibited concomitant medication. The trial schedule of events is included in online supplemental appendix 4.

10.1136/bmjopen-2021-059872.supp4Supplementary data

### Group A

Dexamethasone: Steroids are a backbone of all induction blocks of ALL therapy with dexamethasone, the preferred steroid in the management of patients with ALL (table 1). Initially, dexamethasone was to be administered on a continuous dosing schedule with a weekly total dose of 42 mg/m^2^ for the first course. However, following an observed increase in the risk of infections during the initial stages of the trial, the trial dexamethasone dosing regimen was amended to allow intermittent treatment in blocks rather than continuously, and incorporating a dose reduction from 6 mg/m^2^/day in cycle 1 (d2–4 and D8–11) to 4 mg/m^2^/day during D15–18 and D22–25 of cycle 1. Further dexamethasone is given as a low dose in cycle 2 (D1–4 only: 4 mg/m^2^/day) and then as a high dose again in subsequent cycles (C3–6, D1–5 only: 6 mg/m^2^/day).

**Table 1 T1:** Group A (>18 years) dosing schedule in phase I dose finding

Dose level	**Selumetinib (% of adult MTD**) Cycle 1 D1: single dose Cycle 1 D4–D28: BD dosing Subsequent cycles 2–6: D1-28: two times dosing		**Dexamethasone** Cycle 1 D2–4 and D8-11: 6 mg/m^2^/day, D15–18 and D22–25: 4 mg/m^2^/day Cycle 2 D1–4: 4 mg/m^2^/day Subsequent cycles 3–6, D1–5 only 6 mg/m^2^/day	**Initial design** Applicable prior to DLTs
-1	80%	60 mg two times orally	mg/m^2^*/day orally divided into two doses (as per local practice)	n/a
0	100%	75 mg two times orally		Cohorts 1 and 2
+1†	113%–120%‡	85–90 mg‡ two times orally		Cohorts 3, 4, 5 and 6

*Body surface area for group A to be calculated according to standard institutional practice.

†Important: The selumetinib dose reverts from the +1 dose level to dose level 0 with the start of cycle 2 as patients will only be exposed to a short pulse of dexamethasone which is not expected to substantially affect selumetinib PK.

‡The proposed increase of dose might be changed based on PK results of dose level 0.

DLTs, dose-limiting toxicities; MTD, maximum tolerated dose; n/a, not applicable; PK, pharmacokinetic.

Selumetinib: The dose of 75 mg was chosen as the starting dose for group A (dose Level 0) with the dose only increased if pharmacokinetic (PK) data suggest the addition of dexamethasone decreases selumetinib serum concentrations significantly due to induction of the cytochrome P450 enzyme CYP3A4.^21^

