### Group P

Dexamethasone: As with adult dosing, trial dexamethasone dosing regimen was amended during the initial stages of the trial to be reduced after the first 2 weeks and to be given pulsed during cycle 1 due to the increase in infection risk (table 2).

**Table 2 T2:** Group P (<18 years) dosing schedule in phase I dose finding

Dose level	**Selumetinib (% of adult MTD**) Cycle 1 D1: single dose Cycle 1 D4–D28: two times dosing Subsequent cycles 2–6: D1–28: two times dosing		**Dexamethasone** Cycle 1 D2–4 and D8-11: 6 mg/m^2^/day, D15–18 and D22-25: 4 mg/m^2^/day Cycle 2 D1–4: 4 mg/m^2^/day Subsequent cycles 3–6, D1–5 only 6 mg/m^2^/day	**Initial design** Applicable prior to DLTs
–1	80%	20 mg/m^2^* two times orally	mg/m^2^*/day orally divided into two doses (as per local practice)	Cohorts 1 and 2
0	100%	25 mg/m^2^* two times orally		Cohorts 3 and 4
+1†	113%–120%‡	28–30 mg‡/m^2^* two times orally		Cohorts 5 and 6

*Body surface area for group P to be calculated according to standard institutional practice.

†Important: The selumetinib dose reverts from the +1 dose level to dose level 0 with the start of cycle 2 as patients will only be exposed to a short pulse of dexamethasone which is not expected to substantially affect selumetinib PK.

‡The proposed increase of dose might be changed based on PK results of dose level 0.

DLTs, dose-limiting toxicities; MTD, maximum tolerated dose; PK, pharmacokinetic.

Selumetinib: Results of two paediatric phase I trials using selumetinib only^22 23^ gave the maximum tolerated dose (MTD) as 2×25 mg/m^2^; thus in the SeluDex trial, 20 mg/m^2^ (80% of the single agent MTD of selumetinib) was chosen as the starting dose for safety reasons (dose level -1), specifically for those patients with CNS disease receiving concomitant intrathecal methotrexate.

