#### Phase I

The maximum number of patients to be recruited in phase I is 24; 12 into each group in parallel.

The trial will use the CRM to find which doses to take forward to the phase II activity component of the trial for each group respectively. Each group will use a modified two-stage Bayesian CRM,^27^ recruiting patients in cohorts of two. The design incorporates rules to enable early stopping if the DLT rate at the lowest dose is unacceptably high. Patients are assigned to the starting dose level and follow the initial design (see tables 1 and 2) until the first DLT is observed. Once the first DLT is observed the CRM takes over and determines the ‘best’ dose level that the next cohort should be assigned to, based on the model-based predicted probabilities of toxicity at each possible dose. The acceptable level of toxicity (probability of a DLT) has been chosen to be 17% for each group, that is, the trial will aim to find the highest dose that coincides with this acceptable level. This value was selected based on discussion with clinicians concerning the acceptable rate of DLTs based on the chosen definition.

The stopping rule for toxicity used in the modified CRM is based on the probability of the true DLT rate at the lowest dose being >27%. If based on the observed data the probability of the true DLT rate being greater than this chosen value is >0.85 then the modified CRM will suggest that the trial should stop. The current MTD estimate is calculated after each cohort has been assessed for the full DLT assessment period and the next cohort of patients are then assigned to this MTD estimate. The final MTD estimate calculated after all 12 patients have been treated is the dose estimate to be considered to be taken forward to the phase II component.

This design works relatively well with computer simulations showing a probability for correctly selecting the right dose level of at least 0.6 when the true dose level is 0 or 1, around 0.5 when the true dose level is -1 and at least 0.6 for stopping early when all doses are truly too toxic.

Data will be reviewed at each dose decision stage by the independent TSC. The TSC will incorporate PK results into the decision process; the CRM will advise as to which doses are safe, with the PK additionally informing if there is a need for escalation/de-escalation.

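### Group A: the dosing text opens level +1 only on PK evidence, Table 1 and the CRM text open it on absence of DLTs, and the 0.6 selection probability is not tied to either rule

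*Protocol article*

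**What the plan says.** All places are in the Protocol article.

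- **Interventions, Group A, text below Table 1.** Dose level 0 (75 mg) is the starting dose, "with the dose only increased if pharmacokinetic (PK) data suggest the addition of dexamethasone decreases selumetinib serum concentrations significantly".
- **Table 1, level +1 row (85–90 mg, 113%–120% of the adult MTD).** In the initial-design column, which applies before any DLT, the entry is "Cohorts 3, 4, 5 and 6". Cohorts 1 and 2 are at level 0. The column carries no PK condition. A footnote to the +1 figures reads "The proposed increase of dose might be changed based on PK results of dose level 0". Another footnote returns patients on +1 to level 0 from cycle 2, because the short dexamethasone pulse is not expected to change selumetinib PK much.
- **Statistical analysis plan, Phase I.** "Patients are assigned to the starting dose level and follow the initial design (see tables 1 and 2) until the first DLT is observed". After the first DLT the CRM governs and "the next cohort of patients are then assigned to this MTD estimate", the aim being the highest dose compatible with a 17% DLT rate. Simulations are said to give "a probability for correctly selecting the right dose level of at least 0.6 when the true dose level is 0 or 1". The section ends with the safety committee taking PK into account: "the CRM will advise as to which doses are safe, with the PK additionally informing if there is a need for escalation/de-escalation".

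**The concern.** In the dosing text, the word *only* makes a PK finding a necessary condition for leaving 75 mg upwards. In Table 1 and the first part of the Phase I section, the absence of DLTs (and later the CRM estimate) is sufficient. These are different rules. They part company in an ordinary situation: no DLT in the first two adult cohorts and no material effect of dexamethasone on selumetinib concentrations.

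The rules also answer different questions. The dosing text and the cycle 2 footnote treat +1 as compensation for an interaction. A CRM targeting 17% looks for the highest tolerable dose whether or not there is an interaction. The choice affects the dose given to adults in phase I, the dose that may go forward, and which phase I patients can count towards phase II. It also decides whether the published selection probabilities describe the design actually run.

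**Working it through.** **1. The stated figure.** The 0.6 cannot be reproduced from the article, because the CRM skeleton, the prior and the true-DLT scenarios are not given. It can be neither confirmed nor refuted here. It follows a description of DLT-driven assignment and comes before PK is mentioned in that section, but the article does not say whether a PK condition was simulated.

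**2. The two rules side by side, Group A, no DLT and no PK interaction.**

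| Cohort (2 patients each) | Table 1 and Phase I text | Dosing text |
|---|---|---|
| 1, 2 | level 0 | level 0 |
| 3, 4, 5, 6 | level +1 | level 0 |

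Patients whose level differs: 4 cohorts × 2 = 8 of 12. Size of the step: 85/75 = 1.133 and 90/75 = 1.20, which matches the 113%–120% in Table 1.

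**3. How often the DLT schedule would reach +1 at cohort 3.** With true DLT rate p at level 0, the chance of no DLT in the first 4 adults is (1 − p)^4. For assumed p = 0.03, 0.05, 0.08 and 0.17 this is 0.89, 0.81, 0.72 and 0.47. The situation is therefore not remote.

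**4. Effect of a PK condition on selecting +1.** Let s be the probability of selecting +1 when it is the true level and may be used. Let g be the probability that the PK condition is met, assumed independent of DLTs. Then P(select +1) = g × s.

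- Condition never met: g = 0, so the probability is 0 whatever the skeleton, prior or scenario.
- Otherwise, a result of 0.6 or more needs g ≥ 0.6/s: 1.00 for s = 0.60, 0.86 for s = 0.70, 0.75 for s = 0.80, 0.67 for s = 0.90.

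**5. Illustration under assumed CRM settings.** From the article: three levels, six cohorts of two, target 0.17, stopping if the probability that the lowest-level DLT rate exceeds 0.27 is above 0.85, and the Group A schedule 0, 0, +1, +1, +1, +1. Assumed: power model with a normal prior, selection of the level whose posterior mean DLT rate is closest to 0.17, and no skipping upwards. Exact enumeration gives, for example:

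| Skeleton; prior SD | True DLT rates (−1, 0, +1) | P(correct), DLT-only | P(correct), +1 barred |
|---|---|---|---|
| 0.10, 0.17, 0.25; 1.34 | 0.03, 0.08, 0.17 (true +1) | 0.61 | 0 |
| 0.06, 0.17, 0.33; 0.75 | 0.03, 0.08, 0.17 (true +1) | 0.46 | 0 |
| 0.10, 0.17, 0.25; 1.34 | 0.08, 0.17, 0.30 (true 0) | 0.25 | 0.59 |
| 0.06, 0.17, 0.33; 0.75 | 0.05, 0.17, 0.40 (true 0) | 0.61 | 0.70 |

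Over four assumed skeletons, three prior SDs (0.75, 1.16, 1.34) and several scenarios, the ranges are:

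- true level +1: 0.44–0.90 with DLT-only escalation, 0 with +1 barred;
- true level 0: 0.21–0.61 with DLT-only escalation, 0.59–0.79 with +1 barred, because +1 can no longer be chosen in error.

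The selection probabilities therefore depend materially on the rule, in opposite directions for the two true levels.

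**The case against.** The best defence is that the passages can be read as one procedure. The Phase I section ends with "the CRM will advise as to which doses are safe, with the PK additionally informing if there is a need for escalation/de-escalation". On that reading the CRM settles what is safe, PK settles whether a higher dose is needed, and the safety committee combines them after every cohort. The Table 1 footnotes point the same way by tying +1 to PK. The 8 patients are a ceiling: they require no DLT throughout, no interaction, and a committee that does not hold the dose on PK grounds. The final CRM estimate is also only a candidate for phase II. Finally, the article condenses a longer protocol, to which a PK threshold or simulation settings could properly be left.

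Much of this stands. It rules out calling escalation automatic at the CRM stage, and the missing threshold and settings are not a fault in themselves. It does not remove the conflict. An input that additionally informs a committee is weaker than a condition expressed by *only*, and the footnote says that the increase might be changed, which most naturally concerns its size. No precedence is stated, so the case of no DLT and no interaction still has two printed answers. Condensing explains omissions, not two different rules both in print.

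It can also be said that 0 against 0.6 compares a figure conditional on +1 being right with a state in which +1 is barred. That is fair: the zero is a consequence of the rule, not an estimate of typical performance.

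**Conclusion.** The point holds for Group A. The condition for opening +1 differs between the dosing text on one side and Table 1 with the Phase I section on the other. With no DLT and no interaction, up to 8 of 12 adults would be at a different level, and the recommended phase II dose could differ. That count needs only the cohort size and Table 1. The figure of 0.6 or more need not hold for a true level of +1 under a PK condition, and the article does not say which rule it describes. The zero under a condition that is never met needs no assumptions. The other probabilities rest on the assumed CRM settings, and the g × s relation on independence of PK and DLTs.

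Two stronger readings are tempting but not supported:

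- A reader might infer that the 0.6 cannot be true under both rules. It is stated as a minimum and its inputs are not shown. It could survive a PK condition that is likely to be met, for example g ≥ 0.75 with s = 0.80.
- A reader might extend the conflict to Group P, where Table 2 puts "Cohorts 5 and 6" at +1. The Group P text has no sentence making the increase depend on PK alone, so the same contradiction does not arise there.

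**What to change.** Reconcile the Group A text, Table 1 and the Phase I section so that one rule governs the opening of +1, both in the initial design before any DLT and once the CRM is in use. State which input takes precedence if the CRM and PK point in different directions. State which rule the simulations used. If it is the governing rule, the existing figures can stay. If not, rerun the simulations under the governing rule and restate the selection probabilities.

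The cost is a textual clarification, plus a rerun of existing simulations only in the second case. If the full protocol already states a single rule, the article's wording can be aligned to it. Which rule should govern is for the sponsor and the safety committee. This review does not propose one.
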